**Seattle Angina Scale scoring Scale**

9. In the past 4 weeks, the following limitations were due to chest pain, chest compression and angina:

| activity | Severe restriction | Moderate limitation | Mild limitation | Slightly limited | unrestricted | Limited for other reasons |
| --- | --- | --- | --- | --- | --- | --- |
| Dress oneself | □ | □ | □ | □ | □ | □ |
| Indoor walking | □ | □ | □ | □ | □ | □ |
| shower | □ | □ | □ | □ | □ | □ |
| Climbing or stairs (three floors, non-stop) | □ | □ | □ | □ | □ | □ |
| Do outdoor activities or carry sundries | □ | □ | □ | □ | □ | □ |
| A brisk walk (one kilometer) | □ | □ | □ | □ | □ | □ |
| Jogging (1 km) | □ | □ | □ | □ | □ | □ |
| Lift or move heavy objects | □ | □ | □ | □ | □ | □ |
| Strenuous exercise (e.g. swimming or playing ball) | □ | □ | □ | □ | □ | □ |

10. Episodes of chest pain, chest compression, and angina during maximum intensity activity compared to 4 weeks ago:

□ Significantly increase □ Slight increase □ The same

□ Slight reduction □ Significantly reduce

11. Average number of episodes of chest pain, chest compression, and angina in the past 4 weeks:

□≥4 times/day □ 1-3 times/day □ ≥3 times/week

□ 1-2 times per week □ <1 times/week □ nonseizure

12. Average number of nitrodrugs (e.g. Nitroglycerin, analgesia, etc.) taken for chest pain, chest compression and angina in the past 4 weeks:

□ ≥4 times/day □ 1-3 times/day □≥3 times/week

□ 1-2 times per week □ <1 times/week □ Out of use

13. Trouble with following prescribed medication for chest pain, chest compression, and angina:

□ serious □ moderate □ slight □ Very few

□ There is no □ The doctor did not administer the medicine

14. Satisfaction with various measures for the treatment of chest pain, chest compression and angina:

□ Not satisfied □ Most dissatisfied □ Partial satisfaction

□ Most satisfied □ Highly satisfied

15. Satisfaction with doctor's explanation of chest pain, chest compression and angina:

□ Not satisfied □ Most dissatisfied □ Partial satisfaction

□ Most satisfied □ Highly satisfied

16. Overall, satisfaction with the current treatment of chest pain, chest compression and angina:

□ Not satisfied □ Most dissatisfied □ Partial satisfaction

□ Most satisfied □ Highly satisfied

17. Extent to which joy of living has been affected by chest pain, chest compression and angina in the past 4 weeks:

□ serious □ moderate □ slight □ Very few □ There is no

18. How would you feel if you still have chest pain, chest compression and angina in your future life?

□ Not satisfied □ Most dissatisfied □ Partial satisfaction

□ Most satisfied □ Highly satisfied

19. Heart attack and sudden death concerns:

□ Have been worried about □ Always worry about □ Sometimes worry □ Seldom worry □ Never worry

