**Methodology**

**Study aim and objectives**

This study is order to provide a new therapeutic method for patients with myocardial ischemia-reperfusion injury and reveal the possible mechanism of ECSW for ischemia-reperfusion injury.

The objectives of the study as follows:

**I.** The primary endpoint of this study is 2-year all-cause death, rehospitalization due to cardiovascular disease, major adverse cardiovascular and cerebrovascular events, including cardiac death, myocardial infarction, heart failure, arrhythmia, emergency coronary revascularization, and stroke;

**II.**Secondary endpoints are improvement in angina, quality of life, cardiac structure and function, coronary microcirculation, and expression level of endothelial progenitor cell-derived miR-140-3p.

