**Inclusion and exclusion criteria**

The eligibilities of participants are; ≥18 years old; Acute ST-segment elevation myocardial infarction was diagnosed for the first time, and coronary angiography indicated moderate to severe coronary artery stenosis. PCI was performed within 12 hours of the onset of the disease according to the current guidelines, and the postoperative hemodynamics were stable; CCS angina pectoris grade Ⅱ and above, NYHA cardiac function grade I-Ⅲ; Imaging examination [stress echocardiography and/or stress myocardial perfusion imaging] suggested objective evidence of reversible myocardial ischemia; Voluntary participation, able to cooperate with treatment and follow-up, signed informed consent.

Exclusion criteria will include: unprotected severe left main disease; Left ventricular systolic function was impaired and hemodynamic instability was observed. Poor sound window in ultrasound examination due to chronic obstructive pulmonary disease, bullae, pseudobreast implantation or other reasons; Combined with breast malignancy; Pregnancy; Treatment area skin ulceration or infection; NYHA cardiac function grade Ⅳ; Acute myocarditis, pericarditis, moderate or large pericardial effusion, infective endocarditis, deep vein thrombosis, intracardiac thrombus; Severe aortic stenosis, aortic aneurysm, thoracic aortic dissection, thoracic aortic aneurysm, heart transplantation, metal heart valve replacement, pulmonary embolism; Patients undergoing thrombolysis and surgical bypass; Patients with a history of mental illness, poor compliance and inability to cooperate.

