**Study intervention**

The experimental group will be given extracorporeal cardiac shock wave therapy 2 - 3 days after PCI for acute myocardial infarction, and the treatment course is 3 months. 9 treatments were completed within 3 months as 1 treatment course, 1 week per month, 3 weeks rest, and 3 times of extracorporeal cardiac shock wave will be performed in each treatment week, respectively on the 1st, 3rd, and 5th days of the treatment week, lasting for 3 months in total; The control group received conventional treatment for acute myocardial infarction.

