
**Data collection and follow-up**

All necessary data will be collected and recorded in electronic case report forms for this study, which will be mainly obtained from medical records(such as electronic or paper medical records), local laboratory testing records and investigator’s evaluation on patients. Relevant baseline data will be collected at the time of enrollment in patients with acute ST-segment elevation myocardial infarction reperfusion, mainly including:demography(age, gender, race), medical history, signs, treatment, biochemical values(mainly including serum electrolyte value, serum AST, serum ALT, serum creatinine, serum BUN, serum CK-mb, cTNI, BNP and HsCRP), imaging examination indicators(Echocardiography will be used to measure left ventricular ejection fraction (LVEF), left ventricular end diastolic diameter(LVEDD), global longitudinal strain, myocardial stress changes in each segment and synchrony of myocardial motion, left ventricular contrast echocardiography will assess coronary microcirculation), relevant scale scores(mainly will include 6-minute walk test, Canada Cardiovascular Society (CCS) angina classification, Seattle angina scale (SAQ) score, quality of life scale (SF-8)) (Appendix D) and expression level of miR-140-3p in endothelial progenitor cell (EPCs)-derived exosomes in peripheral blood;Biochemical values, imaging parameters, scores of relevant scales, expression level of miR-140-3p in endothelial progenitor cell (EPCs)-derived exosomes and major adverse cardiovascular events (which will include all-cause death, readmission due to cardiovascular disease, cardiac death, myocardial infarction, heart failure, arrhythmia, emergency coronary revascularization and stroke) will be collected in the test group and control group at 1, 4, 6, 12 and 24 months.

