**Appendix D. Study questionnaire**

**The SF-8 rating scale**

|  |  |  |
| --- | --- | --- |

Date: Serial No

1. In general, in the past 4 weeks, do you think your general health status is:

□ excellent □ Very good □ good □ In general □ poor □ Very poor

2. In the past 4 weeks, has your physical condition limited your ability to do general physical activities (such as walking, climbing stairs, etc.)?

□ No restrictions at all □ A little bit limited □ There are some limitations

□ Very limited □ No physical activity

3. During the past 4 weeks, have you had any health problems carrying out your daily tasks, including going to work and doing housework?

□ It's not difficult at all □ Have a little difficulty □ Have some difficulties

□ Have great difficulty □ Unable to perform routine tasks

4. Have you had any physical pain in the last 4 weeks?

□ No pain at all □ I have a slight pain □ Have a slight pain

□ Have moderate pain □ Have severe pain □ I have very severe pain

5. Have you felt energetic in the past 4 weeks?

□ good □ better □ In general □ poor □ Very poor

6. During the past 4 weeks, to what extent have physical or mental health problems affected your social activities with family and friends?

□ Have no effect at all □ Have little effect □ Have some effect

□ Have a great influence □ You can't socialize

7. In the past 4 weeks, have you been troubled by emotional factors such as anxiety, depression, or irritability?

□ Doesn't bother me at all □ Have mild distress □ Have moderate distress

□ Have a great problem □ Extremely troubled

8. Have you had any personal or emotional problems during the past 4 weeks that have prevented you from carrying out your daily work, school, or other activities?

□ It doesn't affect it at all □ Have a little influence □ Have some effect

□ Have a great influence □ Unable to perform daily activities

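### SAQ and SF-8 baselines look back over four mostly pre-infarct weeks, so improvement from enrolment does not isolate a shock-wave effect

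*Protocol*

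**What the plan says.** In Study aim and objectives, item II reads "Secondary endpoints are improvement in angina, quality of life, cardiac structure and function", followed by coronary microcirculation and the microRNA level. Under Data collection and follow-up, "Relevant baseline data will be collected at the time of enrollment". The baseline set includes the CCS class, the SAQ and the SF-8, and the scales are repeated at 1, 4, 6, 12 and 24 months.

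The timing comes from two other sections. Inclusion and exclusion criteria require a first STEMI with PCI within 12 hours of onset, and also "CCS angina pectoris grade Ⅱ and above". Study intervention gives "extracorporeal cardiac shock wave therapy 2 - 3 days after PCI for acute myocardial infarction", with a course of 3 months.

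The questionnaires are printed in Appendix D. The first SF-8 item begins "In general, in the past 4 weeks, do you think your general health status is", and the other seven use the same window. SAQ item 9 begins "In the past 4 weeks, the following limitations were due to chest pain, chest compression and angina"; items 11 ("Average number of episodes of chest pain, chest compression, and angina in the past 4 weeks"), 12 and 17 use that window too. Item 10 asks for "Episodes of chest pain, chest compression, and angina during maximum intensity activity compared to 4 weeks ago". Items 13 to 16, 18 and 19 state no recall period.

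Data analysis plans between-group comparisons by Welch's t-test or the rank-sum test. It does not say whether the quantity compared is the visit score or its change from baseline.

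**The concern.** Improvement needs a starting point. Here that starting point is a questionnaire answered within days of a first infarct, but worded so that the patient mostly describes the weeks before it. The follow-up questionnaires describe life after the infarct and PCI. The two scores refer to different clinical states, and the state that shock wave is meant to improve, the one just after reperfusion, is hardly represented at baseline.

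A patient without angina before the infarct would score near the best level on the SAQ items with a 4-week window and could hardly improve. A patient with earlier angina could improve because of PCI alone. A change score would then partly sort patients by their history before the infarct. A report that the treated arm improved from baseline could not be credited to shock wave.

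**Working it through.** The protocol gives no figure for the SAQ or SF-8. Its only calculation is the sample size on LVEF (SD 11.7, difference 8.1 read as points, two-sided α 0.05, power 90%). That gives 2 × (1.960 + 1.282)² × 11.7² / 8.1² ≈ 43.8, so 44 per arm as stated. It plays no part in this point.

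**Step 1: latest pre-treatment baseline.** Onset to PCI is 0 to 0.5 day (Inclusion and exclusion criteria). PCI to first treatment is 2 to 3 days (Study intervention). A baseline taken before treatment is therefore at most 0.5 + 3 = 3.5 days after onset.

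**Step 2: share of the recall window before the infarct.** Share = (28 − days from onset to baseline) / 28.

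| Onset to PCI (days) | PCI to baseline (days) | Pre-infarct days | Share |
| --- | --- | --- | --- |
| 0 | 0 | 28 | 100% |
| 0.5 | 0 | 27.5 | 98.2% |
| 0.5 | 2 | 25.5 | 91.1% |
| 0 | 3 | 25 | 89.3% |
| 0.5 | 3 | 24.5 | 87.5% |

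The days before PCI number 28 minus the days from PCI to baseline, so at least 25 of 28 (89.3%).

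**Step 3: follow-up windows.** If the 1-month visit is 28 to 30 days after an enrolment on or after the day of PCI, its 28-day window contains 0 pre-PCI days. The same holds at months 4, 6, 12 and 24.

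**Step 4: what a change score would cost in precision.** Let k be the baseline SD divided by the follow-up SD, and r the correlation between the two scores. Relative to the variance of the follow-up score:

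- change score: 1 + k² − 2rk
- follow-up score adjusted for baseline: 1 − r²

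The difference is (1 + k² − 2rk) − (1 − r²) = (k − r)², which is never negative. The protocol gives neither k nor r. These values are illustrative assumptions:

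| k | r | Change score | Baseline-adjusted |
| --- | --- | --- | --- |
| 1 | 0.2 | 1.60 | 0.96 |
| 1 | 0.3 | 1.40 | 0.91 |
| 0.5 | 0.2 | 1.05 | 0.96 |
| 0.5 | 0.3 | 0.95 | 0.91 |

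A change score is less precise than the plain follow-up score when r < k/2. Under these assumptions its variance runs from slightly smaller to 1.6 times as large. In every row the adjusted comparison has the smallest variance.

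**The case against.** The strongest reply is that the harm presupposes an analysis the protocol does not state. Data analysis names between-group tests and no within-arm test, improvement is one word at the head of a list, and the choice between change and visit score is commonly left to a statistical analysis plan, which is not at hand. This stands as far as it goes: silence on the model is no fault. But the questionnaire wording, the time of baseline and the word improvement are all fixed in the protocol. No later choice of model can make answers about the past four weeks describe the post-infarct state.

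Several stronger readings are tempting, and the protocol does not support them.

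- *The treatment comparison is biased.* It is not. The recall window is the same in both randomised arms, so the effects of infarct, PCI and regression to the mean are shared.
- *The treated arm would appear to improve even if shock wave did nothing.* The direction is unknown. Patients with earlier angina may improve through PCI, while those without may stay level or worsen, and the protocol does not show which group dominates.
- *Precision falls by a known amount, for example 44 per arm counting as 44 / 1.6 ≈ 28.* That needs equal variances (k = 1) and an assumed r of 0.2. A baseline near its ceiling could shrink k, and at k = 0.5 the loss almost vanishes or reverses. The 44 is also an LVEF figure.
- *The CCS baseline is pre-infarct too.* No recall period is stated for CCS, so this cannot be said. Nor are the six SAQ items without a stated window affected in the same way.

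The baseline day is also inferred: the protocol gives none, for controls in particular, and the flow diagram is not shown. Study design asks for no major adverse clinical events in the past 6 months, which is ambiguous. Enrolment long after PCI would, however, contradict the treatment start in Study intervention.

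**Conclusion.** The point holds in a limited form. With a pre-treatment baseline, 87.5% to 100% of the recall window for all SF-8 items and SAQ items 9, 11, 12 and 17 precedes the infarct. The reference time of SAQ item 10 precedes it as well. Every follow-up window is post-PCI, so improvement from enrolment on these items is not a measure of shock-wave effect.

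The consequence is one of interpretation, with a possible loss of precision if change scores are used; its size cannot be derived from the protocol. The between-arm contrast remains valid. The endpoints affected are secondary, and the sample size is untouched. For CCS the reasoning differs: entry requires grade II or above, so regression to the mean can lower the grade in both arms, and again only the comparison between arms is informative.

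The conclusion assumes enrolment between PCI and first treatment, and that the printed questionnaires are used unaltered at baseline. Nothing in the protocol adapts the recall period.

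**What to change.** In Study aim and objectives (item II) and in Data analysis, define the SAQ and SF-8 endpoints as the between-arm difference in score at the post-treatment visits, adjusted for the enrolment score as a covariate. The first scheduled visit after the 3-month course is month 4. Describe the enrolment SAQ and SF-8 as mostly pre-infarct measures, and state that no efficacy conclusion will be drawn from within-arm change.

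For CCS, leave the baseline label as it is and compare the arms at follow-up.

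The cost is wording only. The visits, data and sample size stay the same, and adjustment costs one degree of freedom per model. The downside is small: the report cannot offer a simple statement per arm that patients improved from baseline.
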